#### **4.2.10. Immune-Endocrine and metabolomic mediators assessment (II, IV, V)**

Urine, blood and saliva samples will be collected to assess immune, endocrine and metabolomic assessment markers.

In urine samples metabolomic analysis will be performed with the same protocol described for exhaled breath condensate. But, samples will be collected and immediately frozen at -80°C, then only those samples that have been related to the outcome, respiratory infections in the swimmers cohort or those that completed all protocol of the clinical trials will be used.

Saliva will be collected as previously published[61], subjects will set quietly and with an initial swallow to empty the mouth, un-stimulated whole saliva will be collected by expectoration into a pre-weighted vial for 2 min with eyes open, head tilted slightly forward and making minimal oro-facial movement and saliva flow rate (ml/min) will be determined by weighing saliva density. Duplicate saliva samples can be analyzed for secretory IgA (S-IgA) using ELISA kit. The S-IgA secretion rate will be calculated by multiplying the S-IgA concentration by saliva flow rate

Blood will be obtained by venepuncture from an antecubital vein and will be collected into two Vacutainer tubes containing EDTA, 7ml and two serum-standard tubes 10 ml. Two of the samples with serum and plasma will be centrifuged and then stored -20°C. Hematological parameter, total and differential leukocyte counts will be performed in an automated cell-counter. Lymphocyte subpopulations (CD3, CD4, CD8, CD19, CD56) can be determined by flow cytometry with a three-color flow, in order to enumerate total T cell, T helper, T cytotoxic, B

and NK cells. Side-scatter and forward scatter will be use to gate lymphocyte population by morphology and at least 10 000 lymphocyte events will be acquired per analysis.

Serum Immunoglobulins IgA, IgG, IgM can be measured by nephelometry. Cytokines, IL-1, IL4, IL8 IL-10 also could be measured using commercial ELISA. Insulin, adiponectin, leptin, resistin, tumor necrosis factor- $\alpha$ , serpin/type-1 plasminogen activator inhibitor and interleukin-6 measured by multiplexed bead immunoassay, as previously described[62]. Plasma fatty acids concentration will possibly be analyzed using gas chromatography as previously described[63].

Plasma epinephrine and norepinephrine concentrations might be measured by high-performance liquid chromatography. Plasma adrenocorticotrophic hormone concentrations could be measured by an electrochemiluminescence immunoassay while plasma cortisol concentrations radioimmunoassay will be used.

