#### **4.1.5. Physical activity reduction effect on immune response (V)**

This is a randomized controlled trial where participants, after a run-in period and eligibility evaluation, will be randomized to an intervention consisting in a reduction of physical activity by 50% or maintaining habitual physical activity for two weeks. Participants will be recruited from the same population as the meal-exercise challenge study and stratification will be done accordingly to having asthma and  $BMI \geq 30 \text{ kg/m}^2$  in order for both characteristics could be balanced between groups.

Participants will be at baseline characterized for their nutritional status, dietary habits and physical activity through questionnaire and basal assessment of all sports activity practiced during a week. Also generic quality of life questionnaire will be applied. A pedometer and accelerometer will be used to monitor physical activity. After this run-in period, if they have an adequate physical activity they will be allocated randomly to one of the interventions. Calculation of physical activity reduction will be performed individually, and a daily steps target will be demanded for each group. Both groups will use a pedometer during 3 weeks, except during the night or at circumstances that the device might be damaged (bath). They will be able to monitor if they achieved or exceeded the target number of steps for that day. Keeping the same regular diet without any new changes will be requested and new recall dietary assessment will be also performed in the end of the study. Immune function mediators will be the primary outcome to be assessed before and after the intervention period in both groups. As secondary outcomes endocrine and metabolomic evaluation will be performed.

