### **4.3.3. Acute exercise and meal challenge (IV)**

In the randomized cross-over study, includes all randomized subjects which took at least one meal challenge and exercise intervention and who had at least one post-baseline immune marker variable measurement. Primary and secondary endpoints will be analyzed for the presence of a carry-over effect in the meal challenge study [69].

Changes in the immune biomarkers and endocrine will be presented as mean  $\pm$  standard deviation. Data obtained from high fat and low fat meal challenge will be compared using paired t-tests. Repeated-measures analysis of variance (ANOVA) were used to analyze the effects of the challenges.

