### **4.3.4. Reducing physical activity (V)**

The analysis was conducted using the “intention-to-treat” (ITT) approach, including all randomized subjects which took at least one dose of the study preparation/or intervention and who had at least one post-baseline efficacy variable measurement. Changes between baseline and after intervention period was analyzed with paired t-tests. The absence of studies evaluating the immunological outcomes precluded the power analysis.

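### Urine metabolomics in the trials is limited to an undefined group of protocol completers, which conflicts with the stated analysis sets, chiefly the intention-to-treat set of study V

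*Protocol*

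**What the plan says.** Section 4.2.10 covers studies II, IV and V. Its paragraph on urine says that samples are frozen and then only some are analysed: those linked to a respiratory infection in the swimmers, and for the trials, "those that completed all protocol of the clinical trials will be used". The protocol does not say what completing means.

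The analysis sets are given elsewhere and are wider:

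- **Study V, section 4.3.4:** "The analysis was conducted using the “intention-to-treat” (ITT) approach, including all randomized subjects which took at least one dose of the study preparation/or intervention". A second condition limits this to those "who had at least one post-baseline efficacy variable measurement".
- **Study IV, section 4.3.3:** the analysis "includes all randomized subjects which took at least one meal challenge and exercise intervention". Here too a second condition applies, which keeps only those "who had at least one post-baseline immune marker variable measurement".

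Neither section asks for completion, and neither makes an exception for metabolomics. Section 4.1.5 gives metabolomics formal standing in V: "As secondary outcomes endocrine and metabolomic evaluation will be performed". In IV it is a planned measurement before and after exercise (section 4.1.4).

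**The concern.** Two statements in one protocol give different answers to who is analysed. The narrower one acts at the assay stage, so the intended analysis of urine could be recovered only by going back to the freezer.

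Study V is where this counts. One arm is asked to halve its daily steps and the other to carry on as usual. Completion is determined after randomisation, and section 4.1.5 (Randomization) states that the team is not blinded. Because completion is undefined, who counts as a completer can be decided with the arm known. If adherence is related to the change in a marker, urine results in completers are selected on adherence. They would also describe different people from the immune results of the same trial, while section 4.3.4 labels the analysis intention-to-treat.

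**Working it through.** The plan gives no figure on this point, so there is none to reproduce. The check is first a comparison of the rules and then an illustration of size.

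**Step 1. Who falls between the rules**

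| Participant | Stated analysis set | Urine rule in 4.2.10 |
|---|---|---|
| V: both samples given, protocol completed | in | assayed |
| V: both samples given, judged a non-completer | in (4.3.4) | not assayed |
| V: stopped, no final sample | no final laboratory measurement | nothing to lose from a change analysis |
| IV: one session only | in (4.3.3) | not assayed |

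The second row is the direct contradiction. The fourth is also a contradiction, but section 4.3.3 compares the meals with paired t-tests, which need both periods, so a one-session participant cannot enter that contrast anyway. Only an analysis of samples before and after exercise within one session would lose anything.

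**Step 2. Whether this is only loose wording**

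Section 4.3.2 assigns a completed-protocol analysis to the elderly trial (III). The protocol thus treats completer analysis as a separate approach, and section 4.3.4 gives V a different one.

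**Step 3. What the rule reaches**

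The restriction stands in the urine paragraph. Sections 4.1.4 and 4.1.5 (Intervention) also collect blood and breath condensate, and section 4.2.4 allows the metabolomic analysis to be done in condensate. None of these carries the completer condition.

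**Step 4. Possible size in V**

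From the document: a target of 60 randomised (Summary, Sample Size), in equal numbers (section 4.1.5), so 30 per arm. The remaining inputs are assumptions, because the protocol gives no completion rates: non-completion of 20% or 30% in the reduction arm and 5% in control, and a correlation r of 0.3 to 0.5 between tendency to complete and marker change.

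Dropping the lowest fraction q of a standard normal variable moves the mean of the rest by φ(z_q)/(1 − q):

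- q = 0.05: 0.109
- q = 0.20: 0.350
- q = 0.30: 0.497

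The spurious arm difference with no true effect is the difference of these shifts times r:

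- 20% v 5%: (0.350 − 0.109) × 0.3 to 0.5 = 0.07 to 0.12 SD
- 30% v 5%: (0.497 − 0.109) × 0.3 to 0.5 = 0.12 to 0.19 SD

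At 20% v 5% the numbers analysed are 30 − 6 = 24 and 30 − 1.5 = 28.5. The standard error of an arm difference is √(1/24 + 1/28.5) ≈ 0.28 SD, so 0.07 to 0.12 SD is roughly 0.25 to 0.43 standard errors.

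A cruder model, with loss in one arm only and non-completers 0.5 to 1 SD away from completers, gives a bias equal to the share lost times the gap. That is 0.10 to 0.20 SD at 20% and 0.15 to 0.30 SD at 30%, which is the same order.

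Both calculations count every non-completer as removed by the urine rule. Only those who gave a final sample are, so the rule's own effect is smaller if some gave none.

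**The case against.** The strongest reply is that in V the two sets may nearly coincide. There is one sampling after baseline, and section 4.3.4 already requires a post-baseline measurement. If completing means attending both sampling visits, the urine rule removes almost nobody. No passage makes meeting the step target or returning a diary a condition of completion. This stands as a limit on the size. It does not remove the conflict, because the term is left open and an unblinded team would have to interpret it.

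Four stronger readings are tempting, and the documents do not support them:

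- **All metabolomic results exist for completers only.** The condition covers urine. Condensate and blood are not restricted, and the primary immune markers are untouched.
- **The rule turns the meal comparison in IV into a completer comparison.** The paired t-test already does that.
- **Early stoppers in V have no final visit.** Section 4.1.5 (Intervention) collects the final samples after stating that all participants hand in the pedometer. There is no explicit clause for those who stop early, but that is a separate question of retention.
- **The calculated shift estimates the bias in a planned test.** Section 4.3.4 writes only a paired test of change from baseline and no test between arms. The shift concerns the arm comparison for which V was designed, under assumed inputs.

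It is also fair to say that laboratory work awaits funding (section 9), and that defining completion and labelling the urine analysis as a completer analysis would remove the contradiction. It would not remove the selection.

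**Conclusion.** The contradiction is in the text and should be corrected. It concerns one specimen type, and its main consequence is in V, where urine metabolomics may be selected on adherence and rest on a different group from the immune results. In IV the sets conflict on paper with little effect on the meal contrast.

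The size of any bias is unknown. The range of 0.07 to 0.19 SD is an upper illustration that depends on the assumed 20–30% v 5% non-completion, correlations of 0.3 to 0.5, and a final sample from every non-completer. Against a standard error of about 0.28 SD this is modest. The case for change rests on a plain inconsistency that is cheap to correct.

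**What to change.** In section 4.2.10, delete the completion condition for studies IV and V. State instead that stored urine is assayed for every participant in the sets of sections 4.3.3 and 4.3.4, whether or not step targets were met, and that V is analysed as randomised. If a completer analysis is wanted, define completion in advance and report it as a labelled sensitivity analysis.

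The cost is a change of wording and assays of a few samples already in the freezer. Under the 20% v 5% assumption this is at most 6 + 1.5, or about 7 to 8 participants in V, and fewer if some gave no final sample. No new procedure or visit is needed.

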#### **4.2.11. Physical activity measurement and intervention (IV,V)**

Physical activity will be estimated by: Baecke questionnaire (**Attachment 8**), and International physical activity questionnaire (**Attachment 9**) and by the mean number of steps/day performed during one week assessed by a pedometer.

Baecke questionnaire(**Attachment 8**) is a reliable and valid instrument and has been previously used in the Portuguese population[64, 65]. It is made up of 16 items that call for a Likert-type response (from 1 to 5), designed to assess different categories of the broad concept of physical activity (work/school, sport and leisure). The work/school index was calculate by eight questions (sat,stood, walke, Lifted heavy loads, sweat, work level. Sport index were reported in 4 questions, as well as leisure time index. Total physical activity score could range from 3 to 15. The International Physical Activity questionnaire (IPAQ) (**Attachment 9**) is a general measure of assessment of physical activity and it complements the Baecke questionnaire in physical activity assessment. It is also a valid and reliable measure is several countries including Portugal and has a comparable validity and reliability to the accelerometer and other questionnaires[66].

IPAQ reports separately vigorous-intensity, moderate-intensity and walking in terms of frequency and duration of each specific type of activity, in the past 7 days. This instrument also reports time spent sitting in an ordinary week day. IPAQ will be an expressed according to the guidelines for data processing and analysis in as MET-min/week (metabolic equivalent). After which they will be classified in three categories, low PA level, moderate PA level and high PA [67] .

Physical activity will be evaluated at baseline by two parameter, a pedometer and accelerometer. The accelerometer (Computer Science Application Actigraph), one of the most widely used accelerometers in physical activity research, uses a uni-axial accelerometer that

measures vertical acceleration and deceleration in 1-min epochs. Participants will put it on the right mid-axillary line of the hip on an elastic belt or clip and wear during one week period and then remove it for sleep or any activity that could cause harm to either the monitor or another person. This can be used to monitor light moderate, hard and very hard activity [68]: light intensity will be considered as <3 metabolic equivalents (METs), moderate 3–5.99 METs, hard 6–8.99 METs, and very hard >8.99 METs. Activity counts cut-off, will correspond to MET levels by the equation  $(\text{cnts}/\text{min}) = (5.99 - 1.439008) / 0.000795$  [68]. Pedometer is also a validated method to evaluate physical activity it will be used in association with an accelerometer for baseline physical activity assessment. To register the number of daily steps the subjects will be instructed to wear the pedometer placed in the waistline above the knee, as previously published [29] and it will be worn for 1 week, being removed for sleep or other activity that could damage the device, namely bath.

Pedometer will be further used for intervention of reduced physical activity (V). In this study, accordingly to the previous baseline number of steps per day were instructed to reduce daily steps in more than 50%. For that accordingly to the assessed physical activity in baseline evaluation in those that performed >3500 steps/day, will be recommended to use elevators instead of stairs, riding in cars instead of walking or bicycling during 2 weeks period. A limit of steps/day will be calculated for each participant and they will be able to see if the limit was achieved. All steps will be recorded in the display and stored in the device for posterior computer download.

### 4.3. Statistical analysis (I-V)

All statistic analyses will performed using the SPSS 20.0 software (Chicago, Ill) and Excel, Microsoft Office, for data assembly and graphical analysis. Normality of data distribution will be assessed by the Kolmogorov-Smirnov test, histogram and QQ plot distribution. Results will be expressed as median and inter-quartile range or mean and standard deviation and in discrete variables as count and percentage. If a normal distribution is described t-test-student would then be used in continuous variables. For non-normal data, non-parametric tests, namely Mann-Whitney will be used, to compare groups. Measures with discrete distributions are expressed as counts (%) and analyzed with Pearson-Chi Square or Fisher exact test. The minimum threshold for statistical significance will be  $p \leq 0.05$ . In data with skewed distributions, logarithmic transformation will be done and if appropriate (normal distribution is achieved) comparisons will be made with this change.

#### 4.3.1. Cross-cultural translation and Validation of WURSS (I)

For statistical analysis of questionnaire validation factorial analysis will be used for content validity evaluation using the 7 identified domains of WURSS-21 plus headache, body-ache and fever, which are included in WURSS-24. This approach combines exploratory and confirmatory procedures, using weighted least square estimates employing diagonal weight matrix techniques to seek common factors between the domains; all questioned items will be included in the analysis. Convergent validity will be provided by Pearson correlations between WURSS-21 scores in the first day and SF-36 scores in the third, as this measures health state in the last 4 weeks. For criterion validity sensitivity, specificity and predictive positive values will be calculated, as well as area under the curve. For internal consistency Cronbach's alpha coefficient in each domain based on the average of scores from the first three days will be calculated and also comparison between the first and last day. To evaluate each day, responsiveness index will be calculated which is equal to minimal important differences (MID)/ $\sqrt{(2\text{mean squared error})}$ .

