#### Participants

All patients that require an unscheduled appointment due to acute illness in a primary health care center (USF Progresso, Perafita, Unidade Local de Saúde de Matosinhos) and from the Department of Allergy and Clinical Immunology from Centro Hospitalar de São João will be recruited. The inclusion criteria for respiratory infections cases are: over or equal 16 years of age, physician diagnosis of respiratory tract infections, with onset of symptoms within 48h and with Jackson score for respiratory infections over 3 or higher. In Jackson score eight symptoms (sneezing, nasal discharge, nasal obstruction, sore throat, cough, headache, malaise and chilliness) are classified as 0=absent, 1=mild, 2=moderate or 3=severe and presence of at least one of the first four cold specific symptoms is required for diagnosis. All those patients that attend to the primary care center or allergy department for other reason except respiratory symptoms/infections will be proposed to enroll the study project as controls. Exclusion criteria are: under 16 years of age, all patients with basal or throat symptoms that started more than 48h before they searched medical care. Results provided from patients with allergy and those without allergy complains will be compared for changes in respiratory symptoms score and in quality of life changes.

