#### Procedures

The Wisconsin Upper Respiratory Symptom Survey (**Attachment 1**) is an empirically derived patient-oriented illness specific quality-of-life evaluative outcomes instrument. It is a validated questionnaire in English and is now translated into Spanish, Japanese, French, German, Korean, Russian, and Ukrainian, with high correlation of previous questionnaires aimed to evaluate the presence of upper respiratory symptoms. It is also designed to reflect the impact of colds in quality of life and evaluate the severity through time [9, 37, 38]. This questionnaires correlate with laboratory assessed measures in a induced respiratory infections clinical trial[39]. This is a 21 items questionnaire, based on a 7 point Likert-type severity scale. To those will also be associated the items for headache, body-ache and fever [10, 40]. Questionnaire, WURSS-21 will be given to the included cases and controls, to be completed during 6 days and at the third

day it will be also filled in a validated questionnaire in Portuguese, MOS SF-36 (**Attachment 2**) [41, 42] of quality of life for convergent validity evaluation.

Demographic characteristics (age, gender, education, smoking habits, allergic diseases) will be collected when the questionnaire is delivered, written informed consent will be obtained if the patient decides to fill the questionnaire.

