#### Validation

Content validity of the Wisconsin questionnaire survey was previously studied in the validated versions of WURSS-44 and the short form WURSS-21[9, 38]. In the short form, will be assessed 7 different domains: global day severity, global change since yesterday, cough, throat, nasal, tiredness, functional/activity and other (head congestion). It will be also included

headache, body ache and fever to these domains, which has been used for WURSS-24 [10, 40].

Convergent validity will be assessed by comparison with a health related quality of life questionnaire, SF-36, already validated, which will be filled in at the third day of disease.

For criteria validity, the questionnaire will be compared between patients with respiratory infections and without respiratory infections diagnosed by physicians (which is the gold standard for respiratory infections diagnosis). Furthermore, inclusion criteria use the previously known Jackson criteria widely applied for respiratory infections diagnosis[8]. Both patients will fill WURSS during 6 days and SF-36 on the third day.

Reliability will be evaluated by the application of the same questionnaire through a 6 day period, first three days will be compared using internal consistency measures. As a respiratory infection symptom will change through time (patients will be asked if comparing to the previous day they feel that my cold is very much better, somewhat better, a little better, the same, a little worse, somewhat worse and very much worse) responsiveness to the questionnaire will be evaluated through already published methods[9, 44], namely Guyatt's responsiveness index. This index demands the calculation of Minimal important difference, the mean value of day-to-day changes. Also the mean squared error of the scores will also be needed, which is based on those subjects reporting the same state.

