#### Respiratory infections symptoms questionnaire (I, II)

Respiratory infections symptoms questionnaire has 21 items, organizes in a 7 point Likert-type severity scale (from 1, very mild to 7, severe and one 0, without symptoms). Two items are used to classify the global-severity-today (how sick do you feel today and compared to yesterday I fell my cold is...). The severity score includes 10 items classifying in the last 24h respiratory symptoms (runny nose, plugged nose, sneezing, sore throat, scratchy throat, cough, hoarseness, head congestion, chest congestion, feeling tired) and 9 items of quality of life impact (think clearly, sleep well, breath easily, walk, climb stairs, accomplish daily activities, work outside home, work inside home, interact with other, live your personal life) [10, 40].

An acute respiratory infection episode is defined by having all these items for at least 2 days:

- answering "Yes" to either: "Do you think you have a cold?" or "Do you think you are coming down with a cold?"
- reporting at least 1 of 4 cold symptoms (or synonyms) (nasal discharge (runny nose); nasal obstruction (plugged or congested); sneezing; or sore (scratchy) throat)
- scoring at least 2 points on the Jackson scale (Jackson score is calculated by summing 8 symptom scores (sneezing, headache, malaise, chilliness, nasal discharge, nasal obstruction, sore throat and cough), rated as 0=absent, 1=mild, 2=moderate, and 3=severe.

From the first day of acute respiratory infection day and forward each participant fills out a daily WURSS until they answer "No" to the question "Do you think that you are still sick with this respiratory infection?" for 2 days in a row. The last day the participant answers "Yes" and fills out a WURSS instrument will be the last day classified as acute respiratory infection.

Daily WURSS summary scores are calculated by summing scores of individual item scores, excluding the first and last items, which have categorically different reference domains, and are analyzed separately. Summary scores of ARI illness episodes are calculated by summing daily scores.

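### Study I's convergent-validity test pairs a day-1 cold score with a four-week SF-36 completed on day 3, so a low correlation could not separate a poor translation from the recall mismatch

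*Protocol*

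**What the plan says.** Section 4.3.1 fixes the analysis: "Convergent validity will be provided by Pearson correlations between WURSS-21 scores in the first day and SF-36 scores in the third". The same sentence goes on to give the SF-36's four-week coverage as the reason: "SF-36 scores in the third, as this measures health state in the last 4 weeks".

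The timing comes from three other places:

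- **Entry.** Section 4.1.1, Participants, admits cases "with onset of symptoms within 48h" and excludes patients with "symptoms that started more than 48h before they searched medical care".
- **SF-36 day.** Section 4.1.1, Procedures, places it on the third day of the six-day diary ("day it will be also filled in a validated questionnaire in Portuguese, MOS SF-36"). The Validation paragraph of the same section describes the "SF-36, already validated, which will be filled in at the third day of disease". These are not the same day for a patient who enrols after onset.
- **WURSS window.** Section 4.2.1 states: "The severity score includes 10 items classifying in the last 24h respiratory symptoms".

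Cases and controls both complete WURSS for six days and the SF-36 on day 3 (4.1.1, Validation). Section 4.3.1 does not say whether the correlation is run in cases only or in both groups together.

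**The concern.** Convergent validity asks whether two instruments that should measure the same thing agree. Here one asks about a cold over the last day. The other asks about health over a month, most of which the entry rule places before the cold began. The SF-36 score will then carry a large component of usual health that WURSS is not meant to measure, and the correlation is pulled down for a reason unrelated to the translation.

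The pairing of days adds to this. The Validation paragraph itself expects symptoms to change from day to day, yet the day-1 score is matched to a day-3 form although a day-3 WURSS score is collected.

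The SF-36 is the only comparator named for convergent validity. A sound translation could show a weak correlation. Conversely, a correlation could arise from chronic illness rather than from the cold, because recruitment includes an allergy department and the controls attend for other complaints.

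**Working it through.** The Protocol gives no expected correlation, threshold or sample size for this analysis. The target of 281 in 4.3.1 rests on item prevalence and on sensitivity and specificity, so there is no planned figure to reproduce. The check has two parts.

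**1. Ill days inside the recall window (cases).** Inputs: recall of 4 weeks = 28 days (4.3.1); onset at most 48 h = 2 days before entry (4.1.1, Participants); SF-36 on day 3 (4.1.1).

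- Onset 48 h before entry, day 3 counted from entry: 2 + 3 = 5 days; 5/28 = 17.9%.
- Day 3 counted from onset: 3/28 = 10.7%.

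So 82% to 89% of the window precedes the illness. These are shares of calendar days, not effects on the correlation. Controls attend without respiratory complaints, so the count does not apply to them.

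**2. What this could do to the correlation (illustration; none of these inputs is in the Protocol).** Assume the four-week score is a day-weighted mean of ill-day health and usual health. Let f be the ill share and k the ratio of the ill-day SD to the usual-health SD, with the two components independent. The correlation is then multiplied by

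f·k / √[(f·k)² + (1 − f)²].

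For f = 5/28 and k = 1: 0.1786 / √(0.0319 + 0.6747) = 0.21, so a true correlation of 0.70 appears as 0.15. The same calculation for other values (factor, then apparent correlation):

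| Ill days of 28 | k = 1 | k = 2 | k = 3 | k = 5 |
|---|---|---|---|---|
| 5 | 0.21; 0.15 | 0.40; 0.28 | 0.55; 0.38 | 0.74; 0.52 |
| 3 | 0.12; 0.08 | 0.23; 0.16 | 0.34; 0.24 | 0.51; 0.36 |

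If usual and ill-day health are themselves correlated at ρ, and WURSS relates to usual health only through ill-day health, the factor becomes

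[f·k + (1 − f)·ρ] / √[(f·k)² + (1 − f)² + 2·f·k·(1 − f)·ρ].

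- ρ = 0.3, k = 1: 0.48 (5 days) or 0.40 (3 days), so 0.70 appears as 0.33 or 0.28.
- ρ = 0.5, k = 3: 0.80 (5 days) or 0.71 (3 days), so 0.70 appears as 0.56 or 0.49.

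Part of what is regained in this way comes through usual health, not through the cold.

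A large sample does not help. At n = 281, an observed correlation of 0.15 has a 95% interval (Fisher z) of 0.03 to 0.26. It measures the diluted value precisely and says nothing about why it is low.

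**The case against.** The strongest defence is that day 1 does lie inside a four-week window ending on day 3, so the SF-36 covers the day being correlated. That is true, but days 2 and 3 lie inside it as well, so the recall period gives no reason to prefer day 1.

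Second, respondents may not weight 28 days equally. If recent illness dominates recall, or ill-day variation is large, the dilution is modest. This stands: the factors above run from 0.12 to 0.80, so the size is undetermined. A reader might take 11% to 18% as the attenuation itself, but the documents do not support that.

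Third, no pass mark is set, and validation also rests on factor analysis, sensitivity, specificity and area under the curve against physician diagnosis, Cronbach's alpha, and a responsiveness index. None of these uses the SF-36. This also stands. It rules out saying that a valid translation would formally fail, and it limits the point to one strand of the validation.

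Fourth, controls complete both forms. If the groups are pooled, the case-control contrast enters the correlation and the dilution argument does not carry over directly. Pooling does not rescue the analysis, because group differences and chronic illness could then drive the result in a direction that cannot be predicted from the Protocol.

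**Conclusion.** The point holds for cases, as a matter of interpretation. On the Protocol's own statements, at most about 5 of 28 recalled days (3 on the other reading of day 3) are ill days. The stated reason does not justify pairing day 1 with day 3, and no other section corrects it. A low correlation could not distinguish a poor translation from the recall mismatch.

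A reader might go further and infer that a low correlation would carry no information at all. That is too strong: the dilution depends on assumptions about recall weighting, the relative size of ill-day variation, and the link between usual and ill-day health, and under some of these much of the correlation survives. The ill-day count is firm; the size of the attenuation is not. The change is worth making but does not threaten Study I as a whole.

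**What to change.** In 4.3.1:

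1. Correlate the SF-36 with the WURSS score of the same day (day 3), or with the mean of days 1 to 3, and specify that this is done in cases.
2. Delete the four-week recall as the reason for the pairing.
3. State that, with a four-week form, a low correlation is not evidence against validity.
4. Say whether day 3 is counted from entry or from onset, and use the same definition in 4.1.1 and 4.2.2.

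This needs no new data: WURSS is completed daily for six days, and 4.3.1 already averages the first three days for Cronbach's alpha. The cost is a few sentences and one changed line of analysis.

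A shorter-recall SF-36 would address the mismatch more directly, but the Protocol mentions no such form. It should be used only if a validated Portuguese version exists and the forms have not yet been administered. The second condition is unclear: 4.1.1 places data collection in January to March 2012, before the Protocol's date of 10 December 2012, whereas the milestones put validation at month 34 of a project that began in September 2010. The changes listed above are possible in either case.
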